#### Secondary outcomes

Secondary outcomes include the following:Work ability will be measured using a single item of the Work Ability Index (WAI) [37]. The current work ability compared to lifetime best work ability can be scored on a 0 to 10 response scale, where 0 represents “completely unable to work” and 10 represents “work ability at its best”.Disability will be measured using the Pain Disability Index (PDI). The PDI is a 7-item questionnaire for investigating the magnitude of the self-reported pain-related disability, independent of region of pain or pain-related diagnosis. The PDI measures family/home responsibilities, recreation, social activity, occupation, sexual behavior, self-care, and life support activity. The questionnaire is constructed according to a 0 to 10 numeric rating scale in which 0 means no disability and 10 maximum disability. Total scores can range from 0 to 70, with higher scores reflecting higher interference of pain with daily activities [38, 39].Physical functioning will be measured using the physical functioning subscale of the RAND-36. The questionnaire assesses self-reported physical functioning independent of (pain) diagnosis [40]. The physical functioning scale consists of 10 questions with three possible answers: “yes, limited a lot,” “yes, limited a little,” and “no, not limited at all.” The total score can range from 0 to 100, with higher scores indicating better physical functioning. The validity and reliability of the Dutch version are good [41].Quality of life will be measured using the validated Dutch version of the EuroQol-5D (EQ-5D) [42, 43]. The EQ-5D measures five dimensions: mobility, self-care, activities of daily life, pain and anxiety/depression on a categorical scale (1 to 3). The EQ-5D is a widely employed instrument used to assess health-related quality of life (QoL), and is recommended by the Dutch guideline for health economic evaluations [35]. To allow comparison between several conditions and interventions, Quality Adjusted Life Years (QALYs) will be calculated in three steps. First, the EQ-5D scores (measured at baseline, discharge, 6-month follow-up, and 12-month follow-up) will be converted to utility scores using the Dutch EQ-5D tariff [43]. Second, QALYs will be calculated from three time periods (1 = baseline to discharge, 2 = discharge to the 6-month follow-up, 3 = 6-month follow-up to the 12-month follow-up). Third, one summated QALY will be calculated from the calculated QALYs in step two.

#### Cost outcomes

The following outcomes will be assessed to evaluate the cost-effectiveness of the 40-h VR compared with the 100-h VR:Absenteeism data will be derived from the work participation (that is, primary outcome) data in this study.Presenteeism will be assessed using the presenteeism items of the iPCQ [34]. The questionnaire measures the total days of mental or physical complaints at work, with a recall period of 4 weeks. The amount of work performed accompanied by mental or physical complaints is measured on a 0 to 10 response scale, where 0 represents “I couldn’t do anything,” to 5 “I could do about half of normal,” to 10 “I could do the same as normal.” A population with mental health problems showed good feasibility and validity [34], and moderate reliability for the number of days while impeded by mental or physical complaints (icc 0.56), and a satisfactory reliability for the efficiency rate (0 to 10) item (icc 0.73) [36].Healthcare usage will be assessed using the Trimbos iMTA questionnaire for measuring Costs of Psychiatric Illnesses (TiC-P), module 1 [36, 44]. A recall period of 4 weeks is used in this questionnaire. Visits and consultations of the following healthcare providers were measured: general practitioner, physiotherapist, manual therapist, exercise therapist, occupational therapist, psychologist, insurance physician, medical specialists in hospitals, hospitalization (number of days), occupational physician, social worker, and dietician. Additional items were alternative care, home care, medication use, and job-related care like job coaches, ergonomic changes at the work site and reintegration specialists. Slight adaptations in the context and scope of health care practitioners were made to better match TiC-P to the target population (that is, from psychiatry to pain and work). Another modification was that visits and consultations were measured in both generic and sickness-specific terms. Research shows that health care usage assessment by means of self-reported questionnaires is reliable [45]. A population with mental health problems showed good feasibility, promising construct validity, good agreement on medical resource use (yes/no), and sufficient test-retest reliability on the number of contacts with the health care providers [36]. Until now, reliability of the TiC-P has not been tested in our study population. This needs to be done in the near future.

#### Patient characteristics

Patient characteristics will be collected at baseline (that is, before and during the multidisciplinary screening) to evaluate if randomization resulted in two prognostically comparable groups. The following characteristics will be collected:Demographic variables: age, gender, marital status, nationality, body mass index (obtained from self-reported weight and height), educational level, and health condition [46, 47].General perceived health will be assessed using a single item of the RAND-36 questionnaire [41].Work-related psychosocial factors will be assessed using the Work Reintegration Questionnaire (WRQ). The questionnaire consists of 78 items distributed across eight scales: distress, illness behavior/coping, job strain, job satisfaction, job control, avoidance, perfectionism, and stressful home situation. The questionnaire was developed and validated in Dutch (VAR: vragenlijst arbeidsreintegratie) [48, 49].Self-efficacy of work participation will be assessed on a 0 to 10 response scale. Participants rate the certainty that they will be working in 6 month’s time, where 0 represents “not at all certain” to 10 “extremely certain.” A score of ≥5 is associated with successful work participation after 6 months for workers with subacute back pain [50].Pain intensity and fatigue will each be measured using two questions from an 11-point Numeric Rating Scale, ranging from 0 “no pain/fatigue” to 10 “worst possible pain/fatigue,” requiring patients to rate their worst and average intensity of the last 7 days [51].Work tolerance functions will be assessed at baseline during the multidisciplinary screening using standardized lifting capacity tests from the Functional Capacity Evaluation (FCE) test battery: lifting low and/or overhead lifting. The lifting tests to be assessed depend on the individual’s work tasks. Procedures are described in detail elsewhere [52]. Lifting tests were found to be predictive of work participation in patients with musculoskeletal disorders [53].

### Non-inferiority hypothesis

A reduction in sick leave days of more than 30 days per year is deemed a clinically significant improvement on work participation [15, 17–19, 24]. A difference in sick leave days of 30 or fewer (from the start of the intervention until 12-months follow-up) between 40-h and 100-h VR is assigned as the margin of non-inferiority in this study. Our hypotheses are as follows:H0: μ1 - μ2 ≥30H1: μ1 - μ2 <30

H0 is the null hypothesis, and H1 is the alternative hypothesis, μ1 is the mean number of sick leave days in the 40-h VR group, and μ2 is the mean number of sick leave days in the 100-h VR group.

Non-inferiority is claimed if the upper bound of the one-sided 95 % confidence interval of the treatment effect difference (μ1 - μ2) on work participation does not exceed 30, which means that the risk of it being inferior is within acceptable boundaries [30]. We expect a normal distribution of the primary outcome work participation. If the data on the primary outcome does not follow a normal distribution, we will perform log transformations. The margin of non-inferiority will then be interpreted as a 28 % increase in the sick leave days’ difference of μ1 - μ2. We calculated this percentage as follows:$$ 30/107 = 28\ \% $$

where 30 denotes the margin of non-inferiority and 107 the expected mean days of sick leave in the 100-h VR arm [15, 17–19, 24] during the timing of the data collection, which equals approximately 15.5 months (intervention period of 3.5 months + the follow-up period of 12 months, see Fig. 2).

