### Sample size

A sample size of 174 is calculated to be sufficient (with a one-sided 95 % CI, 80 % power, alpha of 0.025, standard deviation of 80 and a margin of non-inferiority of 30 days) to establish non-inferiority of 40-h VR. The sample size calculation allowed for 15 % loss to follow-up - 10 % expected from comparable studies [18, 59, 60] and 5 % expected due to the extension of the program in the 40-h VR group. An intraclass correlation coefficient (ICC) of 0.05 is accounted for by the use of four rehabilitation centers with two clusters (40-h and 100-h VR) at each center [61, 62]. Because of the difference in program hours between 40-h and 100-h VR, we expect 40-h VR to benefit by 8 extra working days available during the intervention period. We accounted for this in the power calculation by using minus 8 as the expected mean difference between 40-h and 100-h VR. In our power calculation, we assumed a normal distribution of the primary outcome work participation. If the data on the primary outcome does not follow a normal distribution, we will perform log transformations. As previously stated, we will allow 28 % as the margin of non-inferiority when the data is log transformed.

According to the number of patients expected to be referred to the four participating rehabilitation centers per year (approximately 350), and after accounting for two-thirds of non-participation in the study according to Lasagna Law [63], we expect an inclusion of 115 participants per year for this study. Hence, our inclusion period will cover approximately 18 months, and the data collection period will cover 2 years and 9 months.

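### The log-scale fallback with a 28 % margin tests geometric rather than mean sick-leave days, and matches the 30-day margin only at a 100-h mean of 107, so its error rate is not the planned one

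*Protocol article*

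**What the plan says.** All of this is in the protocol article. Under Non-inferiority hypothesis, H0 is a difference of 30 days or more between two arithmetic means: "μ1 is the mean number of sick leave days in the 40-h VR group", with the same definition for the 100-h arm. The section states "We expect a normal distribution of the primary outcome work participation" and then gives the alternative: "If the data on the primary outcome does not follow a normal distribution, we will perform log transformations". For that case, "The margin of non-inferiority will then be interpreted as a 28 % increase in the sick leave"; the sentence goes on to refer this increase to the difference between the two means. The figure is 30/107, "where 30 denotes the margin of non-inferiority and 107 the expected mean days of sick leave in the 100-h VR arm". Under Sample size the switch is repeated: "we will allow 28 % as the margin of non-inferiority when the data is log transformed". The same section plans with "alpha of 0.025, standard deviation of 80 and a margin of non-inferiority of 30 days", and with an expected difference of minus 8 days.

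Under Methodological considerations the margin is justified in days only. Five trials give a mean benefit of 43 days over control care, so a loss of 30 would still leave 13.

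**The concern.** The fallback is a stated, data-triggered replacement of the primary decision rule, with its own margin. Four features do not fit the stated hypothesis.

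- **Estimand.** A difference of mean logs is the log of a ratio of geometric means. The hypothesis, the margin and the effect side of the cost-effectiveness ratio are all in mean days.
- **Margin.** A fixed percentage turns into a number of days that depends on the observed 100-h arm. The justification of the margin is a fixed number of days.
- **Wording.** An increase of 28 % in the difference between the means is not what 30/107 gives, which is 28 % of the 100-h mean.
- **Zeros.** The log of zero is undefined, and the article states no rule for a patient with zero total days.

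At stake is the error rate of the primary claim. A 40-h programme that truly costs 30 mean days could be declared non-inferior more often than planned in some settings, and less often in others.

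**Working it through.** **Inputs from the article.** Margin 30 days; expected 100-h mean 107 days over about 15.5 months; SD 80; alpha 0.025; power 80 %; true difference -8; ICC 0.05; loss 15 %; total 174.

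**1. The plan's own figures.** 30/107 = 0.280, so 28 % reproduces. Per arm, n = 2 × 80² × (1.960 + 0.842)² / (30 + 8)² = 69.6, so 70. Inflating by 1.05 (my reading of how the ICC was used) gives about 74 per arm, 148 in total; 148/0.85 = 174. The stated 174 reproduces with alpha 0.025.

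**2. Is the switch likely?** P(N(107, 80²) < 0) = Φ(-107/80) = 0.091. A non-negative outcome with these moments cannot be close to normal.

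**3. Geometric against arithmetic means.** For a log-normal outcome, geometric mean = mean × exp(-σ²/2), with σ² = ln(1 + SD²/mean²). The ratio tested is therefore (m1/m2) × exp[(σ2² - σ1²)/2]. At true means of 137 and 107, a loss of exactly 30:
- Equal CV: 1.28, on the margin.
- Equal SD of 80: σ1² = 0.293 and σ2² = 0.444, so 1.280 × exp(0.075) = 1.38, beyond the margin (stricter).
- SD 120 against 80: 1.20, inside the margin (laxer).

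**4. The margin in days.** 0.28 × 60 = 16.8; 0.28 × 107 = 30; 0.28 × 150 = 42. At 150, 43 - 42 leaves about 1 day of the benefit over control care, against the 13 that the article relies on. There, a true 30-day loss is a ratio of 180/150 = 1.20, inside the margin.

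**5. False-pass rate at a true 30-day loss.** Simulation with 74 per arm, one-sided 0.025, 20,000 trials per setting and no centre effect. The log test uses a t-interval on log days against ln(1.28) = 0.247; the day-scale test uses a t-interval on days against 30. Log-normal shape, unequal spreads and 100-h means other than 107 are assumptions.

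| Setting | Log test | Day-scale test |
|---|---|---|
| 100-h mean 107, equal CV | 2.7 % | 3.2 % |
| 100-h mean 107, equal SD 80 | 0.4 % | 2.1 % |
| 100-h mean 60, equal CV | 0.05 % | 3.4 % |
| 100-h mean 150, equal CV | 8.3 % | 2.9 % |
| 100-h mean 150, equal SD 80 | 5.8 % | 2.3 % |

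With days capped at what the period can hold (about 336 working days, 15.5 × 52/12 × 5, or 471 calendar days), a 100-h mean of 107 and a 100-h log-SD of 0.75 before capping:

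| 40-h log-SD | Log test, cap 336 | Log test, cap 471 |
|---|---|---|
| 0.75 | 1.5 % | 2 % |
| 0.85 | 3.6 % | 5 % |
| 0.97 | 8 % | 13 % |
| 1.10 | 16 % | 27 % |

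The day-scale test stays at about 2-3.5 % in these cases.

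**6. Cost of staying on the day scale.** Power at -8 days (log-normal, CV 0.75) is 84.9 % on the day scale and 83.7 % on the log scale, so nothing is lost.

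**The case against.** Much can be said for the plan. The trigger, the transformation and the 28 % are all written down in advance, and the analyst is blinded. A reader might infer that the margin is chosen after seeing the results; the article does not support that. Only which branch applies depends on the data. The displayed formula also makes the intended meaning of 28 % plain, so the wording about the difference is a slip to correct and no more.

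The fallback is not uniformly lax. At the planned mean with equal CV it is nominal. With equal SD, or at a lower 100-h mean, it is stricter.

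A reader might also infer a far larger error. If the two geometric means are equal and the whole 30-day loss sits in a longer 40-h tail, the log test passes about 44-45 % of trials. That needs a log-SD of 0.97 on a geometric mean of 85.7, which is a 40-h SD of 171 days, more than twice the planned 80. It also puts 7.9 % of patients above 336 days and 3.9 % above 471. The outcome cannot produce this, so the figure should not be used.

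The same holds for claims that zeros would destroy power. The article gives no share of zeros, everyone is on sick leave at inclusion, and extrapolation between time points may make exact zeros rare. The choice of offset may sit in an analysis plan that is not shown. What stands is that zero totals are not excluded, since counting starts about 1.5 months after baseline, and that the log is undefined for them.

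None of this removes the change of estimand or the floating margin.

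**Conclusion.** The concern holds, as something that should be fixed. The fallback is likely to be triggered, answers a question about geometric means that the hypothesis does not ask, and agrees with the 30-day margin only when the 100-h mean is 107 and the log-variances are equal.

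At a true 30-day loss and one-sided 0.025, the false-pass rate is 0-3 % at a 100-h mean of 107 or below with equal CV or equal SD. It is about 4-28 % when the 40-h arm has the larger log-spread (0.85-1.10 against 0.75), and about 5-9 % at a mean of 150 with equal relative spread or equal SD. These rates rest on the assumed log-normal shape, spreads and means. The statement that the error rate is not the planned one does not depend on them.

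The article also gives a one-sided 95 % interval as its decision rule, which does not match alpha 0.025. That is a separate matter, but at 0.05 the two uncapped rates at a mean of 150 become 14.2 % (equal CV) and 10.7 % (equal SD).

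**What to change.** Under Non-inferiority hypothesis and Sample size, delete the log transformation and the 28 % as a decision rule. Keep the difference in mean days and the 30-day margin whatever the distribution, estimated from the mixed model already planned under Effectiveness. If residuals are skewed, take the upper confidence limit from robust standard errors, or from a bootstrap stratified by centre and arm and run within the multiple imputation. Report any log-scale ratio as a sensitivity analysis only, and state there how zero totals are handled.

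The cost is a few sentences and a little extra programming. The bootstrap planned for the economic evaluation does not transfer directly to a multilevel model on imputed data, and resampling by arm alone would ignore centre.

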### Statistical methods

All statistical analyses will be performed at the patient level, with descriptive statistics being used to compare the baseline measurements of the two intervention groups. If necessary, analyses will be adjusted for baseline differences. All analysis will be performed according to the intension-to-treat principle and the per protocol principle [30, 54]. To claim non-inferiority, both intention-to-treat and per protocol analysis must show non-inferiority [54]. Missing data on costs and effects will be assessed using multiple imputation techniques [25]. The imputation technique will depend on the results (that is, missing completely at random, missing at random, or missing not at random).

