#### Effectiveness

The primary outcome work participation will be analyzed in three steps. Step 1. For every time point (that is, T0 - T8, see Fig. 2), we will present the number of sick leave days as an absolute number and as a percentage related to contract hours/month, in which the absolute number and percentages between a given time point and the preceding time point will be calculated using linear extrapolation, as recommended [36, 44, 55]. Step 2. We will calculate and present the cumulative total days of sick leave per month from the start of the intervention until the 12-month follow-up using an area under the curve for all measurement points, in which the number of sick leave days between a given time point and the preceding time point will be calculated using linear extrapolation. Step 3. Linear mixed models with multilevel analyses will be performed to assess non-inferiority between the two groups at the 12-month follow-up (that is, intervention period and 12-month follow-up) by means of 95 % confidence intervals (that is, the CI approach). To improve generalizability and comparability of this study with other studies, we will repeat step 3 at the following time intervals: I) discharge to 12-month follow-up; II) start of intervention to 6-month follow-up; III) discharge to 6-month follow-up. These additional analyses will contain no conclusions about non-inferiority and will be analyzed in the “classical” superiority manner.

A t-test or Mann–Whitney U test (in the case of no normal distribution) will be used to examine differences at discharge, at 6-month follow-up, and at 12-month follow-up (defined as the difference in outcome between baseline and last follow-up) in all secondary outcomes between the intervention groups. We will perform these analyses on superiority, thus without margins of noninferiority, as this is only relevant for the analysis of the primary outcome.

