### Randomization

An independent statistician prepared the randomization by using computer-generated randomization tables. To prevent unequal randomization, employees are pre-stratified by duration of sick leave (short-term <6 weeks or long-term ≥6 weeks) and whether they are on full-time (100 %) or part-time (≤99 %) sick leave. Block randomization with blocks of four will be applied to ensure equal group sizes within each stratum. A separate block randomization table is generated for each of the four participating vocational rehabilitation centers. For each stratum, the researcher will prepare opaque, sequentially numbered, and sealed coded envelopes, with a note for either the 40-h VR or 100-h VR. After the multidisciplinary screening (at baseline), the multidisciplinary screening team and rehabilitation physician will fulfil all study criteria. If participants meet all criteria, they will be allocated to 40-h or 100-h VR. Treatment allocation will be performed by a member of the multidisciplinary screening team (MST) at each center and can be performed at the center or via telephone (this will differ among the centers). The MST member hands over two envelopes (left over) of that stratum, and the patient is asked to pick one of the envelopes, open the envelope and sign the note. In the case of telephone allocation, the MST member will ask the patient to sign informed consent and to return it via a reply envelope. When the signed informed consent is received, the MST member will perform the treatment allocation without the patient. After randomization, a research assistant will make an appointment for the patient’s first intervention date.

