### Methodological considerations

The first methodological consideration of this study is that we were not able to fulfil the recommended steps for the composition of a margin of non-inferiority [30, 65]. This was because there is currently no historical data, such as meta-analysis, comparing the 100-h vocational rehabilitation with usual care. However, our non-inferiority margin is based on results from five randomized controlled trials evaluating multidisciplinary vocational rehabilitation compared with control interventions (that is, usual care, such as occupational physician, physical therapist, occupational therapist, *etcetera*) [15, 17–19, 24]. These studies found 43 days as the mean difference ((41.9 + 53.7 + 42 + 60.5 + 17.5)/5) in days on sick leave after one year follow-up in favor of multidisciplinary vocational rehabilitation. Consequently, we have decided that 30 is an acceptable margin of non-inferiority. One can argue that this limit is too wide, and that claiming non-inferiority could be achieved too simply, but for claiming non-inferiority, the upper bound of the one-sided 95 % confidence interval of the treatment effect difference (40-h VR – 100-h VR) must be 30 or less. Furthermore, when the margin of non-inferiority of 30 is reached after 12 months follow-up, this is in fact 13 days (43–30) better than if a patient had been referred to usual care (occupational physician, physical therapist, occupational therapist, *etcetera*). A mean saving of 10 sick days per year is considered the smallest effect that would be clinically worthwhile [66]. We therefore consider 30 as a reasonable margin of non-inferiority. The second methodological consideration of this study is the slight differences between the participating rehabilitation centers. For instance, each center has its own logistic restrictions, such as a restriction in intervention facilities (that is, equipment, building); and centers have evolved their own methods over the years. This may lead to interpretation issues in analyzing the blended results of the four centers. However, we solved this problem by multilevel analyses and by performing both interventions at each center, that is, by randomizing at the participant level. Although performing both interventions at the center level may introduce contamination, we consider that the advantages of randomization at the participant level outweigh the disadvantages of contamination.

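### Adjustment is conditional on observed baseline differences, two stratification factors enter no stated analysis, and secondary outcomes use unadjusted change scores: precision is lost and an analytic choice is left open.

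*Protocol article*

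**What the plan says.** All references are to the protocol article.

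- **Statistical methods.** The arms are first compared at baseline, "with descriptive statistics being used to compare the baseline measurements of the two intervention groups". The rule that follows is "If necessary, analyses will be adjusted for baseline differences". The section gives no threshold for necessity and no list of covariates.
- **Patient characteristics.** Baseline data are collected "to evaluate if randomization resulted in two prognostically comparable groups", which is a check on randomization and not a covariate plan.
- **Randomization.** The section states that "employees are pre-stratified by duration of sick leave" and by full-time or part-time sick leave. Centre is a third factor: "A separate block randomization table is generated for each of the four participating vocational rehabilitation centers".
- **Effectiveness, primary outcome.** "Linear mixed models with multilevel analyses will be performed to assess non-inferiority between the two groups". No stratum or baseline covariate is named. Methodological considerations adds, on differences between centres, that "we solved this problem by multilevel analyses and by performing both interventions at each center".
- **Effectiveness, secondary outcomes.** A t-test or Mann-Whitney test is used at discharge, 6 months and 12 months, on a measure "defined as the difference in outcome between baseline and last follow-up) in all secondary outcomes between the intervention groups".

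**The concern.** Two stated rules use the design and the baseline data poorly.

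First, whether the primary analysis is adjusted depends on how the arms happen to look at baseline, and nobody has said what would count as a reason to adjust. Stratification tends to balance sick-leave duration and type, so a rule triggered by imbalance will tend not to select them. Yet they describe the baseline state of the primary outcome. Leaving them out keeps their variance in the residual and makes the interval wider than the design allows.

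Second, the secondary tests subtract the baseline value instead of regressing on it, and they use none of the three stratification factors.

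Non-inferiority is decided by one upper confidence limit against 30 days, and both the intention-to-treat and per-protocol analyses must pass. Interval width and a fixed model therefore matter. The secondary outcomes are superiority comparisons outside that claim, so for them only efficiency is at stake.

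**Working it through.** **Inputs from the Sample size section.** SD 80, margin 30 days, expected difference -8, alpha 0.025, power 80 %, total 174, 15 % loss, ICC 0.05. **Assumed, because the documents do not give them:** R2 of the added covariates (0.1 to 0.3) and baseline-outcome correlation r (0.3 to 0.7).

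**1. The plan's own figure.** n per arm = 2 × [80 × (1.960 + 0.842)/38]² = 69.6. Taking the ICC as a flat 5 % inflation and dividing by 0.85 gives 69.6 × 1.05/0.85 = 85.9, so 86 per arm and 172 in total, close to 174. How the ICC was actually applied is not stated. The calculation uses the full SD of 80, so no gain from covariates is credited.

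**2. Primary outcome, illustration.** Evaluable patients: 174 × 0.85 = 148, or 74 per arm. SE = 80 × sqrt(2/74) × sqrt(1 - R2), with no ICC allowance. Power at -8 = Phi(38/SE - 1.96). Half-width = 1.96 × SE, in line with the stated alpha of 0.025.

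| Assumed R2 | SE | Half-width (days) | Power at -8 |
|---|---|---|---|
| 0 | 13.15 | 25.8 | 82 % |
| 0.1 | 12.48 | 24.5 | 86 % |
| 0.2 | 11.76 | 23.1 | 90 % |
| 0.3 | 11.00 | 21.6 | 93 % |

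An R2 of 0.2 is worth 148/0.8 = 185 evaluable patients. R2 here means variance explained beyond centre, which the multilevel model already carries.

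**3. Secondary outcomes.** Let s0 and s1 be the baseline and follow-up SDs. The change-score variance is s0² + s1² - 2·r·s0·s1, and the ANCOVA variance is s1²(1 - r²). The difference is (s0 - r·s1)², which is never negative. With equal SDs the ratio of ANCOVA to change score is (1 - r²)/[2(1 - r)] = (1 + r)/2:

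- r = 0.3: 0.65 (35 % lower)
- r = 0.5: 0.75 (25 % lower)
- r = 0.7: 0.85 (15 % lower)

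This compares means, so it applies to the t-test. It does not carry over exactly to the Mann-Whitney test.

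**4. The open choice.** A simulation used 8,000 runs per setting, 74 per arm, one normally distributed covariate and nominal one-sided error 0.025. Type I error was taken at a true difference of 30, and power at -8. Values are for r = 0.3/0.5/0.7.

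| Strategy | Type I error | Power |
|---|---|---|
| Never adjust | 0.025/0.026/0.026 | 83/82/82 % |
| Always adjust | 0.026/0.025/0.026 | 86/91/98 % |
| Adjust only if the baseline test is significant | 0.023/0.021/0.020 | 83/83/84 % |
| Report whichever result passes | 0.033/0.040/0.043 | 87/92/98 % |

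Adjustment triggered by imbalance did not inflate error, but it gave up most of the available power. Inflation appeared only when the choice followed the result.

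**The case against.** The strongest reply has five parts.

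- **Centre is not ignored.** The primary analysis is multilevel and the article says this handles centre differences. This stands. For the primary outcome the gap is confined to the two sick-leave factors.
- **The baselines are used.** Change scores take in each outcome's own baseline and give a valid comparison in a randomized trial. This also stands. The weakness is inefficiency, not error.
- **The trigger is the baseline comparison, not the outcome.** The analyst is blinded to allocation, and both analysis populations must pass. A reader might infer that the rule inflates type I error. The documents do not support that: they nowhere propose choosing the result that passes, and the simulated imbalance rule was slightly conservative. What remains is that, without a criterion, the choice is not fixed in advance.
- **The gain cannot be sized from the documents.** This stands. R2 and r are assumptions. The 82 % starting point is also slightly above the planned 80 %, because it carries no ICC allowance.
- **Covariate lists often belong in an analysis plan.** True, and a missing list alone would not be a point. But the article states a conditional rule and a specific secondary test, and those are what should change.

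Two further inferences go too far. The article does not say that the strata were chosen as prognostic; its stated reason is to prevent unequal randomization. Nor do weekly contract hours strictly limit the outcome, because sick leave is measured in working days.

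**Conclusion.** The point holds as one of efficiency and prespecification. The adjustment rule depends on observed imbalance and has no criterion. Sick-leave duration and type enter no stated analysis. The secondary tests omit all strata and use the less precise of two available methods.

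The estimate is not biased, and omitting the strata makes the interval conservative. A reader might take this as a threat to the non-inferiority conclusion itself. At the planned difference, however, the expected upper limit without adjustment is -8 + 25.8 = 17.8 days, well below 30.

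The cost is power: about 4, 8 or 11 percentage points at assumed R2 of 0.1, 0.2 or 0.3. For secondary outcomes it is a variance saving of 35 to 15 % forgone at assumed r of 0.3 to 0.7, given equal SDs at baseline and follow-up. For r below 1 and equal SDs the direction of the secondary loss is certain; only its size is assumed.

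**What to change.** Delete the conditional clause in Statistical methods. State that the primary multilevel model, with centre retained, always includes arm, sick-leave duration stratum, full-time/part-time stratum and T0 sick leave as prespecified covariates. Contract hours may be added, if named in advance. Use the same covariates in the intention-to-treat and per-protocol analyses, and keep the baseline table descriptive.

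For secondary outcomes, replace the t-test and Mann-Whitney test on change with ANCOVA at each time point, or one mixed model over T2, T5 and T8, adjusted for the baseline value of the outcome and the strata.

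The cost is analysis wording only. The strata are known at randomization, sick leave and every secondary outcome are measured at T0, and contract hours are already needed for the descriptive percentages. No patient, visit or measurement is added.
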